### Design

2.2

The present RCT (*N* = 600) was designed to evaluate the efficacy of a novel, military-relevant, ACT-based resilience training that we refer to as Psychological Flexibility Training and that we developed for this project. The primary goal of this intervention is to enhance resiliency and optimize readiness in military personnel. For the proposed study, it is hypothesized that the ACT principles will also improve the psychological health outcomes by reducing symptoms of anxiety, depression, and posttraumatic stress disorder (PTSD) in military operational settings, as suggested by the Cochrane Database of Systematic Reviews on Psychological Interventions for Resilience Enhancement in Adults (14). We have two primary research hypotheses. First, we hypothesize that military personnel who receive psychological flexibility training will demonstrate a statistically significant increase in psychological resiliency compared to military personnel receiving training as usual over the course of the study. Second, we hypothesize that military personnel who receive Psychological Flexibility Training will demonstrate a statistically significant increase in psychological resiliency after completing a military operational deployment compared to a group of military personnel receiving military resilience training as usual. Military training as usual for the Army is Master Resilience Training, which is the resilience enhancement component of the broader Comprehensive Soldier Fitness Initiative (32). Of note, all participants receive Master Resilience Training as part of their training as usual. Thus, the current study is testing the incremental value of adding Psychological Flexibility Training.

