##### Connor-Davidson resilience scale

2.6.1.1

The CD-RISC (34, 35) is a 25-item questionnaire examining attitudes toward coping with adversity. The shorter, 10-item questionnaire is being administered for this study. The CD-RISC is the primary outcome measure for this study.

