### Data analytic plan

2.7

The primary outcome to address study aims is the change score difference between group (psychological flexibility vs. treatment as usual) on the Connor-Davidson Resilience Scale (CD-RISC) over time. Analyses will be intent-to-treat using data from all randomized participants regardless of the extent of participation. The statistical analysis model is a mixed-effects regression with repeated measures using all assessment time points. Advantages of likelihood-based regression models over conventional ANOVA include the ability to use data from all participants even if they only have baseline data, relaxation of the assumption of equal variances, specification of data distributions other than normal, and the ability to analyze longitudinal data in the presence of missing data. Models will include the fixed effects of group, time, and the respective two-way interaction. Deployment history will also be entered into models as a covariate. Random intercepts and slopes will be tested, and covariance structure selection will be based on likelihood criteria model comparisons (e.g., Akaike’s Information Criteria). Little’s (1988) missing completely at random test and regression-based sensitivity analyses will be used to investigate the nature of missingness and the appropriateness of likelihood-based modeling (54). We will also derive and report on minimally important difference metrics on the CD-RISC (55, 56). Supplementary analyses of the other measures will use the same statistical analysis design. We will report on minimally important change and reliable change indices for the Posttraumatic Stress Disorder Checklist-5 (PCL-5), for which these metrics have been established (55, 57). We will assess deployment history at all time-points and will use this as a covariate in all pre-post analyses. All tests will be two-tailed with unadjusted *p* = 0.05. Analyses will be done using the LME4 package using R statistical software.

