#### Addressing hypotheses

2.7.2

The first research question relates to the pre-post training effect of workshop participation. Analyses will be based on changes during the 4 months before and following the training and will analyze data from all randomized participants. The second research question relates to the effect of training on change during deployments. Analyses will use data only from deployed participants. As deployments occur at varied points in time and are variable in duration, the selection of the baseline and post-deployment assessments for these analyses will be based on the deployment dates of each participant.

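### Two primary hypotheses are each tested at an unadjusted two-sided 0.05 with no rule linking them, so the error of an either-one-succeeds claim exceeds 5%

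*Protocol article*

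**What the plan says.** Section 2.2 (Design) states: "We have two primary research hypotheses". The first predicts "a statistically significant increase in psychological resiliency compared to military personnel receiving training as usual over the course of the study". The second predicts "a statistically significant increase in psychological resiliency after completing a military operational deployment", again against training as usual. One instrument serves both: "The CD-RISC is the primary outcome measure for this study" (section 2.6.1.1).

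Section 2.7.2 (Addressing hypotheses) gives each hypothesis its own analysis. For the first: "Analyses will be based on changes during the 4 months before and following the training and will analyze data from all randomized participants". For the second: "Analyses will use data only from deployed participants", with the before and after assessments chosen from each participant's own deployment dates.

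Section 2.7 (Data analytic plan) fixes the level for everything: "All tests will be two-tailed with unadjusted" *p* of 0.05. It describes the analyses of the other measures as supplementary. Nowhere does the article rank the two primary hypotheses, divide alpha between them, make one conditional on the other, or require both to succeed. It does not state a family-wise error rate.

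**The concern.** Two primary tests, each at 0.05, give the trial two chances of a positive primary result. The tests differ in population and time window, so they are not the same test reported twice. They share arms, construct and outcome measure, and the Conclusion (section 3) speaks of a single determination of whether the programme works, with possible adoption in other units if it does. The article does not say which hypothesis has to succeed for that determination. As written, either could be used.

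If so, the error rate that matters to someone deciding on adoption is the chance that at least one of the two is falsely significant, and that is larger than the level of each test. This is more than a detail the article leaves open: it takes an explicit position on multiplicity, and that position covers both primary tests.

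**Working it through.** **Inputs from the protocol article.** Two primary hypotheses (2.2); each tested two-sided at 0.05, unadjusted (2.7); test 1 in everyone randomized, test 2 in the deployed only (2.7.2). The 0.05 is a chosen level, so there is no derived figure to reproduce.

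**Not given.** The correlation r between the two test statistics, and the share f of participants who deploy. Both are treated as unknown below.

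**Formula.** With both nulls true and each test holding its level,

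family-wise error = 1 − P(|Z1| < 1.96 and |Z2| < 1.96), with (Z1, Z2) bivariate normal with correlation r.

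At r = 0 this is 1 − 0.95² = 0.0975. Whatever r is, it cannot exceed 0.05 + 0.05 = 0.10.

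| r | Family-wise error |
|---|---|
| 0 | 9.75% |
| 0.3 | 9.51% |
| 0.5 | 9.07% |
| 0.7 | 8.35% |
| 0.8 | 7.81% |
| 0.9 | 7.04% |

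The error is 9% or more while |r| is at most about 0.53. It approaches 5% only as the two tests become identical.

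**Which r is plausible?** Assume that CD-RISC scores at any two visits have the same correlation ρ and equal variance (set to 1). A change score then has variance 2(1 − ρ).

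- Windows that share no visit: covariance ρ − ρ − ρ + ρ = 0, so correlation 0.
- Windows that share one visit: covariance of size 1 − ρ, so correlation of size (1 − ρ) / [2(1 − ρ)] = 0.5.

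Because test 2 uses only a share f of the participants in test 1, the correlation of the test statistics is the change-score correlation times √f (participants treated as independent for this step). With f = 0.5, for example, 0.5 × √0.5 = 0.354, which gives 9.42%. So under the separate windows of section 2.7.2, |r| lies between 0 and 0.5 and the error between 9.1% and 9.75%.

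**A reading with more overlap.** Section 2.2 frames hypothesis 1 across the whole study, while section 2.7.2 analyses the months around training. If the section 2.2 reading governs and most participants deploy, the two tests share much more information. At the extreme of identical change scores, r = √f: f = 0.5 gives r = 0.707 and 8.31%; f = 0.75 gives r = 0.866 and 7.34%. For r of 0.8 to 0.9 the error is 7.8% to 7.0%, lower but still above 5%.

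**Check of the remedies.**

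- Fixed sequence: if both nulls are true, a false claim requires the first test to reject, so the error is 5%.
- 0.025 each: 1 − 0.975² = 4.94% if independent, and at most 5.0%. Holm also holds 5%.

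**The case against.** The strongest reply is that the two hypotheses are different research questions: the effect of the workshop, and the effect during deployment. If each is reported as its own claim, each carries its own 5% error, and whether distinct questions need joint control is partly a matter of judgement. The article does not say in words that either success would establish efficacy. This stands as a condition on the finding. It does not remove it, because arms, construct and outcome are shared, one efficacy conclusion is drawn, and no rule stops that conclusion from resting on whichever test succeeds.

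A second reply is that a fixed sequence also runs each test at 0.05, so the quoted sentence does not exclude one, and the order could be in an analysis plan that is not shown. That is possible. But a statement that all tests are unadjusted reads most naturally as no multiplicity control, and if an order exists the sentence misdescribes it.

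Three stronger readings are tempting and are not supported:

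- That the error is 9% to 10% without qualification. The correlation is not given, and heavy overlap brings the figure to 7% to 8%.
- That the plan promises 5% family-wise and fails to deliver it. It promises only 0.05 per test.
- That this inflation comes on top of inflation from group randomization. The calculation assumes that each test holds its own level; how clustering is handled is a separate question.

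Nor does the point extend to the remaining measures, which section 2.7 already labels supplementary. The Conclusion also presents the trial as a first step, which tempers the stakes.

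**Conclusion.** The concern holds, with conditions. The plan tests two primary hypotheses on one outcome at an explicitly unadjusted 0.05, with no rule connecting them. The chance of at least one false primary claim is then about 9% to 9.75% for r up to about 0.5, and about 7% to 8% for r of 0.8 to 0.9.

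These figures rest on three assumptions: both nulls are true, success on either test would be claimed as efficacy, and each test on its own holds its 0.05 level. If both tests had to succeed there would be no inflation, but the article sets no such rule. The lower overlap, and so the higher figure, fits the analyses as section 2.7.2 describes them.

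**What to change.** Replace the unadjusted rule, for the two primary tests only, with a family-wise procedure fixed before results are seen. Either would do:

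- **Fixed sequence.** For example, hypothesis 1 in everyone randomized at two-sided 0.05, then hypothesis 2 in the deployed at 0.05 only if hypothesis 1 is significant. This follows the order in which the article lists them and leaves hypothesis 1 its full level. The cost is that hypothesis 2 cannot be confirmatory if hypothesis 1 fails. Since the trial's rationale stresses operational stress, the sponsor may prefer the reverse order; that is the sponsor's choice.
- **Holm, or 0.025 each,** if both must be claimable independently. The cost is power. Take the article's d = 0.30 with 300 per arm. Ignoring clustering, a move from 0.05 to 0.025 lowers power from 95.7% to 92.4%. If clustering has already brought it down to exactly 80%, the same move lowers it to about 71% (normal approximation). The level of 0.025 is also the strictest Holm applies, so Holm loses no more than the split.

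Neither option needs more participants. The text is a sentence or two, but sections 2.2 and 2.7.2 must first agree on the time span of hypothesis 1, because an ordered test needs a single definition. The other measures can stay supplementary, as section 2.7 already has them.

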#### Power analysis

2.7.1

Statistical power estimates were obtained from the PASS15 software (NCSS, 2017) modules for comparison of two means or two proportions in a cluster randomized design. Estimates were obtained for a range of standardized mean differences (Cohen’s *d*) from 0.35 to 0.50, which range from modest (*d* = 0.35) to medium in size (*d* = 0.50). Effect sizes below 0.35 are unlikely to be clinically significant and *d* = 0.50 is often considered to be a threshold for a meaningful difference. We also estimated the reduction in Failure % that was detectable at 0.80 assuming a base rate of 80%. We specified a total of 12 clusters of 50 participants for a total *N* = 600. The proposed sample size (*N* = 600) provides statistical power of at least 80% to detect a standardized mean difference (or change over time) in the “small to moderate” range (Cohen’s *d* of 0.30). This applies not only to analyses involving the entire randomized sample but also for analyses based on subsamples based on factors such as deployment, demographics, or other military service characteristics.

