**Method/design:**

This study will evaluate the efficacy of a two-day training program based on ACT for fostering psychological flexibility, the central target in ACT, for enhancing resiliency, and for preventing the development of psychological health symptoms. The research participants will be a non-clinical population of active duty military personnel (*N* = 600). The ACT-based training program (*n* = 300) will be compared to a military resiliency training as usual, known as Master Resilience Training (*n* = 300). Assessment measures will be administered at the baseline assessment, after training, prior to a military deployment, and after returning from a deployment. Qualitative interviews will be conducted to provide feedback on the training program.

**Clinical Trial Registration:** NCT05094115.

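### Power is claimed at d = 0.30, below the 0.35 to 0.50 range that the section says was computed and below its own relevance threshold, with all 600 participants counted

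*Protocol article*

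**What the plan says.** All of this is in the protocol article. Section 2.7.1 (Power analysis) reports estimates from software modules for cluster randomized designs, over effect sizes "from 0.35 to 0.50, which range from modest" to medium. It adds: "Effect sizes below 0.35 are unlikely to be clinically significant". The design entered is stated as "We specified a total of 12 clusters of 50 participants", which makes 600. The conclusion is that this sample "provides statistical power of at least 80% to detect a standardized mean difference (or change over time", at a Cohen's d "of 0.30). This applies not only to analyses involving the entire randomized sample".

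The section also reports a second calculation on a binary scale: "We also estimated the reduction in Failure % that was detectable at 0.80 assuming a base rate of 80" per cent.

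Two further inputs come from elsewhere. The abstract gives equal arms: "The ACT-based training program (*n* = 300) will be compared" with 300 on training as usual. Section 2.7 (Data analytic plan) fixes the test: "All tests will be two-tailed with unadjusted *p* = 0.05". Section 2.2.1 randomizes groups rather than individuals.

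**The concern.** The concluding effect size does not fit the paragraph that leads to it. A value of 0.30 lies outside the range said to have been computed and below the threshold the authors set for a worthwhile effect. A reader cannot tell whether 0.30 came from the cluster calculation, from another calculation, or from a slip.

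This matters because a cluster design with 6 groups per arm is sensitive to the ICC, so moving from 0.35 to 0.30 is not harmless rounding. Counting all 600 as analysed pushes in the same favourable direction. If the claim is too generous, readers will credit the trial with more sensitivity to small effects than it has.

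The Failure % calculation has a related problem. The primary outcome is change on the CD-RISC, and neither Table 1 nor section 2.7 defines a failure endpoint, so that calculation supports no stated analysis.

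**Working it through.** **Inputs from the article.** 12 clusters of 50, taken as 6 per arm because the arms are equal (300 and 300); two-sided 0.05; power 80%; d = 0.30 with SD 1.

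**Assumed inputs.** ICC values of 0 to 0.05 and a 20% loss. The article gives neither, so they are shown as ranges or examples.

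**Formulas.** Design effect DE = 1 + (m - 1) x ICC, with m participants per cluster. Noncentrality = d / sqrt(2 x DE / n), with n = 6m per arm. Two reference distributions were used: the normal, and t with 12 - 2 = 10 degrees of freedom, the cluster-level count. For 80% power the required noncentrality is 1.960 + 0.842 = 2.80 (normal) or about 3.11 (t, 10 df).

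**The plan's own figure.** It cannot be reproduced, because power in this design depends on an ICC that the article does not print. The check is therefore to find the ICC at which the claim just holds.

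**Step 1, limit with all 600.** Without clustering, 80% power at d = 0.30 needs 2 x 2.80² / 0.30², about 175 per arm. So 300 per arm tolerates DE of about 300 / 174.4 = 1.72, and ICC = 0.72 / 49 = 0.0147. With 10 df, DE = (0.30 / 3.11)² x 300 / 2 = 1.396, and ICC = 0.396 / 49 = 0.0081.

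**Step 2, limit with an assumed 20% loss (m = 40, n = 240).** Normal: DE = 240 / 174.4 = 1.376, ICC = 0.376 / 39 = 0.0096. With 10 df: DE = (0.30 / 3.11)² x 240 / 2 = 1.117, ICC = 0.117 / 39 = 0.0030.

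**Step 3, power at d = 0.30 and detectable d at 80% power (normal / t with 10 df).**

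| ICC (assumed) | Power at d = 0.30, m = 50 | Detectable d, m = 50 | Detectable d, m = 40 |
|---|---|---|---|
| 0 | 95.7% / 91.1% | 0.229 / 0.254 | not tabulated |
| 0.01 | 85.3% / 77.4% | 0.279 / 0.310 | 0.302 / 0.335 |
| 0.02 | 74.3% / 65.4% | 0.322 / 0.357 | 0.341 / 0.379 |
| 0.05 | 50.7% / 43.2% | 0.425 / 0.472 | 0.439 / 0.488 |

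**Step 4, the range said to have been computed.** With all 600, the largest ICC that keeps 80% power is 0.027 / 0.018 at d = 0.35 and 0.077 / 0.059 at d = 0.50. Lowering the claim from 0.35 to 0.30 therefore roughly halves the tolerable ICC: 0.027 to 0.015 (normal), or 0.018 to 0.008 (10 df).

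**Step 5, analysis of change.** If d is scaled on the raw-score SD and the analysis is of change, the variance is multiplied by 2(1 - r), where r is the baseline-follow-up correlation (not stated). With all 600 and d = 0.30, the ICC limit (t, 10 df / t, 598 df) is 0.008 / 0.015 at r = 0.5, 0.015 / 0.023 at r = 0.6, 0.027 / 0.038 at r = 0.7, and 0.051 / 0.067 at r = 0.8.

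**The case against.** The strongest reply is that nothing here shows the figure to be wrong. At ICC zero the full sample has 91% to 96% power at d = 0.30, and at least 80% power at 0.30 implies at least 80% across 0.35 to 0.50, so the two statements do not conflict numerically. That stands: the article cannot be shown to contain a calculation error. It does not explain why the conclusion uses an effect outside the range reported and below the stated threshold.

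A second reply is that a journal article may leave the ICC and attrition rate to the full protocol, and that the cluster modules named need an ICC or an equivalent as input. That also stands. A reader might infer that clustering was ignored or that the ICC entered was close to zero; the article does not support either inference, and the unprinted ICC carries no weight on its own. The attrition point is narrower: 600 is both the enrolment total and the number in the power statement.

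A third reply is that the primary analysis is a repeated-measures model of change, and the power sentence mentions change over time. Step 5 shows that this can loosen the limit to roughly 0.03 to 0.07 at r = 0.7 to 0.8. The ICC limits in steps 1 and 2 therefore belong to a standardized mean difference, the quantity the sentence names first.

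On loss, hypothesis 1 uses the 4 months before and after training rather than the whole 16 months, and the likelihood-based model keeps participants with partial data. Both soften the point, but missing post-baseline scores still carry no outcome information.

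Finally, a reader might connect the 80% base rate with the washout rate of about 80% for a special forces course in the Introduction. Nothing in the article makes that link. The minimally important difference and reliable change metrics planned in section 2.7 could be dichotomised into a failure outcome, but the article does not say so.

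**Conclusion.** The point holds as an unsupported and internally inconsistent power statement, not as a demonstrated arithmetic error. That 0.30 lies outside the reported range and below the section's own threshold follows from the text alone.

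The size depends on assumptions. For a standardized mean difference with 6 clusters of 50 per arm, the claim needs an ICC of at most about 0.015 (normal) or 0.008 (10 df), and about 0.010 or 0.003 if 20% are lost. A reader might go further and say that the trial is really powered only for effects of about 0.36 to 0.47. The article does not support that as a fact: those are the 10-df values at assumed ICCs of 0.02 and 0.05, the normal values are 0.32 to 0.43, and no document says which ICC is usual for this scale in Army units. A high baseline correlation would move all of these in the trial's favour.

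The statement should be corrected, since it describes the trial's sensitivity and restating it is cheap.

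**What to change.** In section 2.7.1, reconcile 0.30 with 0.35 to 0.50. Replace the concluding sentence with the detectable d that the cluster calculation gives for 12 clusters of 50, stating:

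- the ICC actually entered;
- cluster-level degrees of freedom (10);
- an attrition allowance;
- whether d is scaled on the raw score or on change, with the assumed baseline correlation if change is used.

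Show the result over a range of ICCs, in the form of the table above. Drop d = 0.30 if that calculation does not support it. The next sentence, on subsamples, refers back to the same figure and should be reworded to match.

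Either tie the Failure % calculation and its 80% base rate to a defined outcome, or remove it.

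This is a wording change with no added enrolment. Its only cost is a stated figure that may be less favourable.

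### Power of at least 80% at d = 0.30, stated for all 600 participants, is extended to subsamples of any size, and primary hypothesis 2 is tested in such a subsample

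*Protocol article*

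**What the plan says.** Section 2.7.1 (Power analysis) takes its estimates from software modules for cluster-randomized comparisons of two means or two proportions. It fixes the size: "We specified a total of 12 clusters of 50 participants for a total *N* = 600". It says that this sample "provides statistical power of at least 80% to detect a standardized mean difference (or change over time") at a Cohen's d of 0.30. It then carries the claim over to subsets: "This applies not only to analyses involving the entire randomized sample but also for analyses based on subsamples based on factors such as deployment". The same sentence goes on to name demographic and military service factors. The article gives no ICC, no expected number deployed and no minimum subsample size.

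Section 2.2 (Design) says "We have two primary research hypotheses". The second concerns resiliency after an operational deployment. For that question, section 2.7.2 (Addressing hypotheses) says "Analyses will use data only from deployed participants". Section 2.7 (Data analytic plan) sets the test level: "All tests will be two-tailed with unadjusted *p* = 0.05".

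**The concern.** With effect size, test level and ICC held fixed, power falls as the number analysed falls. A figure derived for 600 participants therefore cannot be passed to subsets without saying how large they are.

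The sentence does more than decorate a secondary analysis. One of the two primary hypotheses is tested only in deployed soldiers, and this carry-over is the article's only statement of power for that test. If the deployed set is a half or a quarter of the sample, a non-significant result for hypothesis 2 could be read against a stated 80% power that the design does not provide. The same applies to any demographic or service subgroup reported under the claim.

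**Working it through.** **Inputs from the article.** Two-sided test at 0.05 (section 2.7); d = 0.30, 12 clusters of 50, 600 in total (section 2.7.1); 300 per arm (Abstract), so 6 clusters per arm.

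**Assumptions, because the article gives no value.** ICC from 0 upwards, shown mainly at 0 and 0.01; deployed share, shown as 75%, 50% and 25%; arms of equal size within each subset.

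**Formulas.** With n per arm and m per cluster, the design effect is DE = 1 + (m − 1) × ICC, and the noncentrality is λ = d / √(2 × DE / n). Power comes from the normal distribution, or from a noncentral t with (clusters − 2) degrees of freedom.

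**Step 1: the article's own figure.** It can only be bounded, since no ICC is given. For all 600 at d = 0.30:
- ICC 0: λ = 0.30 / √(2/300) = 3.67; power 0.957 (normal) or 0.911 (10 df).
- ICC 0.01: DE = 1 + 49 × 0.01 = 1.49; λ = 3.01; power 0.853 or 0.774.
- ICC 0.02: DE = 1.98; λ = 2.61; power 0.743 or 0.654.

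So the 80% claim holds for the full sample only if the ICC is at most 0.0147 (normal) or 0.0081 (10 df). Also, d = 0.30 lies outside the 0.35 to 0.50 range for which section 2.7.1 says estimates were obtained.

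**Step 2: smallest sample with no clustering.** n per arm = 2 × (1.960 + 0.842)² / 0.30² ≈ 174.4, or 175.4 by the t test. Rounded up, that is 176 per arm, 352 in total, and 352 / 600 = 58.7%.

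**Step 3: power at d = 0.30 in subsets spread over all 12 clusters.**

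| Share kept | N | ICC 0: normal / 10 df | ICC 0.01: normal / 10 df | d detectable with 80% power (normal), ICC 0 / 0.01 |
|---|---|---|---|---|
| 100% | 600 | 0.96 / 0.91 | 0.85 / 0.77 | 0.23 / 0.28 |
| 75% | 450 | 0.89 / 0.82 | 0.78 / 0.69 | 0.26 / 0.31 |
| 50% | 300 | 0.74 / 0.65 | 0.65 / 0.56 | 0.32 / 0.36 |
| 25% | 150 | 0.45 / 0.38 | 0.41 / 0.35 | 0.46 / 0.48 |

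Half-sample example at ICC 0.01: m = 25, DE = 1 + 24 × 0.01 = 1.24, λ = 0.30 / √(2 × 1.24 / 150) = 2.33. With 10 df, the effect detectable in a half sample is about 0.40 at ICC 0.01 and 0.44 at ICC 0.02; the normal values are 0.36 and 0.39.

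**Step 4: whole units deploy.** If six whole clusters deploy (3 per arm, m = 50), DE stays at 1.49 for ICC 0.01, λ = 0.30 / √(2 × 1.49 / 150) = 2.13, and power is 0.57 (normal) or 0.37 (4 df).

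**Step 5: share needed for 80% power at d = 0.30, spread over 12 clusters.** By the normal approximation: 58% at ICC 0, 68% at ICC 0.005, 81% at ICC 0.01. With 10 df: 72% and 87%; at ICC 0.01 it is not reached even with all 600. If the full sample has exactly 80% power (ICC 0.0147, normal), every proper subset falls below: 90% of the sample gives 0.775 and 50% gives 0.608.

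**Step 6: no deployment figure is needed to refute the sentence.** Splitting 600 by any factor leaves at least one part with 300 or fewer. By step 3, that part has at most 0.74.

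**The case against.** The best counter-argument is that the deployed share is unknown and may be large. Section 2.3.1 starts recruitment in a unit that deploys regularly, and with an ICC near 0 a share above about 59% (72% with 10 df) would still give 80% power. This stands: for the deployed set, the claim is unsupported rather than disproved. It does not save the sentence, which sets no size condition and covers demographic and service subsets too.

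A second argument is that baseline information may help. If d = 0.30 is on the raw standard deviation and the analysis uses change scores with an assumed pre-post correlation of 0.7, d on the change scale is 0.30 / √(2 × 0.3) = 0.387. Then 210 participants suffice at ICC 0, and a half sample has 0.92 power at ICC 0, or 0.77 at ICC 0.01 with 10 df. So the 352 threshold belongs to the two-means model. But that is the module the article names, it attaches d = 0.30 to change over time as well, and it states no correlation. Even at 0.7, a quarter sample has only 0.66 at ICC 0, and one of the three rank strata in section 2.4 must hold 200 or fewer.

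Third, section 2.7.1 itself regards effects below 0.35 as unlikely to matter clinically. At d = 0.35 a half sample has 0.86 at ICC 0, and 0.78 (normal) or 0.69 (10 df) at ICC 0.01. The shortfall is smaller there, but the figure the article carries over is for 0.30.

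Finally, whole-unit deployment is only a scenario: section 2.7.2 describes deployments at varied times. The full protocol may also give an expected number deployed; it is absent only from this article.

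**Conclusion.** The concern holds. As a general statement, the carry-over of 80% power at d = 0.30 to subsamples is false under the two-means model that the article names: at least one subset of every split has power of 0.74 or less before clustering is counted. For the deployed set that carries primary hypothesis 2, the stated power has no basis in the article. If half deploy, power is 0.74 at ICC 0 (normal); at ICC 0.01 it is 0.65 or 0.56 when deployers are spread over the clusters, and 0.57 or 0.37 when six whole clusters deploy (normal or t). If a quarter deploy, it is 0.45 at ICC 0 (normal), and 0.41 or 0.35 at ICC 0.01. These figures rest on assumed ICCs and deployed shares, equal arms and no gain from baseline. A high deployed share with an ICC near 0, or a strong pre-post correlation, would narrow or close the gap for hypothesis 2, but the article states none of these.

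**What to change.** Delete the carry-over sentence from section 2.7.1. In its place, give the effect detectable with 80% power for the deployed set, as a small table over:
- the expected deployed fraction (for example 25%, 50% and 75%);
- deployment scattered over all clusters or by whole units;
- ICC from 0.01 to 0.05.

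State the assumed ICC, the degrees of freedom used and, if a gain from baseline is claimed, the pre-post correlation. Say that demographic and service subsamples are exploratory and will be reported as estimates with confidence intervals.

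The cost is wording only. Design, recruitment and conduct are unchanged, but the stated power for hypothesis 2 will probably be less favourable.
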